## Abstract

**Background:**

Cervical cancer is caused by Human Papilloma viruses (HPV) and is preceded by precursor stages: Cervical Intraepithelial Neoplasia (CIN). CIN is mostly found in women in their reproductive age and treated with a Loop Electrosurgical Excision Procedure (LEEP). The recurrence or residual disease rate after treatment is up to 17%. These women have a lifelong increased risk of recurrent CIN, cervical cancer and other HPV related malignancies. Furthermore, LEEP treatments are associated with complications such as premature birth. Limited data show that prophylactic HPV vaccination at the time of LEEP reduces recurrence rates, therefore leading to a reduction in repeated surgical interventions and side effect like preterm birth.

The primary study objective is to evaluate the efficacy of the nonavalent HPV vaccination in women with a CIN II-III (high-grade squamous intraepithelial lesion (HSIL) lesion who will undergo a LEEP in preventing recurrent CIN II-III after 24 months.

**Methods:**

This study is a randomised, double blinded, placebo controlled trial in 750 patients without prior HPV vaccination or prior treatment for CIN and with histologically proven CIN II-III (independent of their hrHPV status) for whom a LEEP is planned. Included patients will be randomised to receive either three injections with nonavalent (9 HPV types) HPV vaccine or placebo injections (NaCL 0.9%) as a comparator. Treatment and follow-up will be according the current Dutch guidelines. Primary outcome is recurrence of a CIN II or CIN III lesion at 24 months. A normal PAP smear with negative hrHPV test serves as surrogate for absence of CIN. At the start and throughout the study HPV typing, quality of life and cost effectiveness will be tested.

**Discussion:**

Although prophylactic HPV vaccines are highly effective, little is known about the effectivity of HPV vaccines on women with CIN. Multiple LEEP treatments are associated with complications. We would like to evaluate the efficacy of HPV vaccination in addition to LEEP treatment to prevent residual or recurrent cervical dysplasia and decrease risks of repeated surgical treatment.

**Trial registration:**

Medical Ethical Committee approval number: NL66775.078.18. Affiliation: Erasmus Medical Centre. Dutch trial register: NL 7938. Date of registration 2019-08-05.

## Background

Worldwide, cervical cancer is diagnosed annually in more than 500,000 women and is still a major health problem among women worldwide [1]. Cervical cancer is preceded by Cervical Intraepithelial Neoplasia (CIN) of the cervix and caused by high risk Human Papilloma Viruses (hrHPV) [2]. CIN is subdivided in three groups: CIN I mild dysplasia, also known as low grade squamous intraepithelial lesion (LSIL). CIN II is mild dysplasia and CIN III severe dysplasia, both also known as high-grade squamous intraepithelial lesion (HSIL). Persistent hrHPV infection is a prerequisite to develop cervical cancer. About 80% of women will be infected with HPV during their life and most women are able to clear the HPV infections. However, approximately 20% of these women have detectable transient infections and a fraction will subsequently develop to cervical cancer if not treated for these precursor lesions [3]. With adequate screening and treatment of CIN, cervical cancer can be prevented [4].

The most commonly used method to treat CIN II-III is Loop Electrosurgical Excision Procedure (LEEP) to prevent possible progression to invasive cancer. Data on recurrent disease after LEEP vary in the literature. Up to 17% of women treated for CIN II-III have residual or may develop recurrent CIN II-III [5, 6]. Treatment is associated with side effects such as hemorrhage, infection, and stenosis of the cervix, and as well as adverse pregnancy outcomes, such as premature rupture of membranes and premature birth. Re-excision is needed in case of recurrence with an increased risk for adverse events. Especially the adverse obstetrical outcomes are higher after multiple treatments [7–9]. Women treated for CIN also have an increased risk of developing cervical, vaginal and vulvar cancer compared to patients with normal primary smear test results [10–12]. To prevent HPV-related diseases, eradication is preferable to treating recurrences repeatedly [13]. Recurrence can be monitored by HPV testing.

Many studies have proven the efficacy and safety of the prophylactic HPV vaccine against the development of cervical intraepithelial neoplasia in HPV naïve women [14–16]. In 2013, Kang et al. reported retrospective data that demonstrated possible prevention of CIN II-III recurrence after LEEP treatment when treatment was combined with quadrivalent HPV vaccination. This study showed that 5 patients (2.5%) in the vaccinated group (197 patients) and 18 patients (8.5%) in the unvaccinated group (211 patients) developed recurrent disease after LEEP (relative risk 0.17, 95%CI 0.08–0.36; *P* < 0.001) related to the vaccine HPV types. Irrespective of HPV vaccine type the recurrence rate was 2.5% (9/360) in the vaccinated group versus 7.2% (27/377) in the unvaccinated group. Multivariate analysis showed that no vaccination after LEEP was an independent risk factor for recurrent CIN II-III (HR = 2.8; 95% confidence interval 1.3–6.0; *P* < 0.01) [17]. Previously, Joura et al. concluded from post hoc analysis, women receiving prophylactic HPV vaccine in a randomized setting and treated for HPV related diseases (cervical, vaginal, vulvar) are less likely to develop recurrent lesions compared to those not vaccinated [18]. There is increasing evidence of an additional vaccine effect after treatment of clinical HPV related anogenital, dermal and oropharyngeal diseases [17, 19–22]. Hypothetically, an increased immune response with increasing levels of antibodies after HPV vaccination might explain the effect. In addition, there ought to be protection against de novo HPV infections [23, 24]. A randomised controlled trial is lacking on this subject.

In this study, we will compare HPV vaccination with the nonavalent HPV vaccine (types 6, 11, 16, 18, 31, 33, 45, 52, and 58) versus placebo (physiological salt solution) vaccination subsequently to LEEP treatment in women without previous treatment for CIN or HPV vaccination. This study is a randomised, double blinded, placebo controlled trial to evaluate the efficacy of the nonavalent HPV vaccine in preventing recurrent CIN II-III after 24 months.

## Methods

### Setting and study design

The VACCIN study is a randomised multicenter, double blinded, placebo controlled trial in female patients with histological diagnosed CIN II or CIN III and treated with LEEP. Recruitment of participants will be done from colposcopy clinics in participating centers. After histologic diagnosis of CIN II-III for which a LEEP is necessary, patients will be counselled for participating in this study.

In the Netherlands most women with CIN are detected via population based cervical cancer screening starting at the age of 30 years.

In addition, general practitioners may refer women with intermenstrual or postcoital bleeding. This also includes women younger than those in the national screening program for cervical cancer. When abnormal Pap smears are found, they are referred for colposcopy.

### In- and exclusion criteria

Women are eligible for participation if they are eighteen years old or above, histologically proven CIN II or III and will be treated with a LEEP. Inclusion must be within four weeks after LEEP. Exclusion criteria are: a prior HPV vaccination, invasive carcinoma, immune-compromised women, pregnant women, prior treatment for CIN-lesions, insufficient understanding of the Dutch language or allergic to vaccine components.

### Randomisation, blinding and treatment allocation

Randomisation will be performed through the secure web-based interface Castor EDC (Castor Electronic Data Capture, available at: https://castoredc.com). Patients will be randomised to either active study medication, or placebo in a 1:1 ratio. Randomisation will be stratified by age, categorized as being 18 to 29 years, 30 to 44 years, or 45 years and older. Women aged 18 to 29 years are not eligible for routine screening under the national screening program. The second stratum includes women of 30 to 44 years who are of reproductive age and invited for routine testing under the national screening program. The third stratum women of 45 years and older, who are less likely to be fertile. Randomisation will use random permuted blocks of sizes 2 and 4.

Both doctor and patient will be blinded for treatment allocation. The allocated medication will be prepared and distributed by the hospital pharmacy as syringes with identical appearance.

### Study objectives and outcome

The primary objective is:

The efficacy of nonavalent HPV vaccination in women with a CIN II-III lesion who underwent a LEEP in preventing recurrent CIN II-III after at 24 months follow-up.

The secondary objectives are:
The recurrence of CIN I-II-III at 6, 12 and 24 months.The effect of HPV vaccination on HPV DNA presence at 6 and 24 months after LEEP.The effect of HPV vaccination on Pap-smear results.Number of LEEP for recurrent CIN.Cost-effectiveness analysis from a societal perspective: intramural and extramural medical costs questionnaire (iMCQ) and productivity cost questionnaire (iPCQ) will be performed at the start of the study, at 2 months and after 24 months.Quality of life will be assessed with quality of life questionnaire: Euroqol 5D-5 L at the start of the study, at 2 months, at 6 months and after 24 months.Side effects and adverse events. One week after each vaccination, a telephonic interview will be performed to ask for side effects after the injection.

The tertiary and long-term objectives are:
Cytology result after 5 years by retrieving HPV-test and Pap smear results from the national database of the population based cervical cancer screening program.Cytology result after 10 years by retrieving HPV-test and Pap smear results from the national database of the population based cervical cancer screening program.Vaccination effect on premature delivery and obstetrical complications by comparing the results to a national database on childbirth data.

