### Data collection

All data will be collected using an eCRF and by means of electronic questionnaires. The eCRF and questionnaire data will be collected and stored using Castor EDC, which is also used for randomisation. Subject numbers will be assigned sequentially to subjects enrolled in the study. Stored data is only accessible to the principal and coordinating investigator.

The following data and outcome parameters are collected (see also Fig. 2):
Patient characteristics; age, obstetrical history, contraceptive use, condom use complementary to contraceptive, HPV related history, smoking, family planning.Indication for testing, cytology results, KOPAC-classification, HPV genotype, biopsy result.Quality of life questionnaire (Euroqol 5D-5 L) and societal economical costs questionnaire (iPCQ, adjusted iMCQ).Initial Pap smear and HPV test results

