**Fig. 2 Fig2:**
[figure not shown]
Schedule of enrolment, interventions, and assessments VACCIN-study. * Follow up is according to national guideline, when needed cytology, HPV typing or colposcopy is performed and data is collected between 6 and 24 months. ** When result at 24 months is either HPV positive or ≥ PAP2 a colposcopy is performed

1 week follow-up:
Side effects of the injection, Result of LEEP (no CIN, CIN I, II or III) and LEEP margins (clear margins or CIN in margins).

2 months follow up:
Side effects of the injection.QoL (Euroqol 5D-5 L) and societal economical costs questionnaire (iPCQ, adjusted iMCQ).

6 months follow-up:
Cytology results and HPV genotype, QoL (Euroqol 5D-5 L) questionnaire.Side effects of the injection.

24 month follow-up:
Cytology results and HPV genotype. When either test is abnormal, colposcopy will be performed and biopsies taken for histologic study endpoint.QoL and societal economical costs questionnaire (iPCQ, adjusted iMCQ).All other cytology test, colposcopy results, LEEP result and HPV genotype test between appointment 6 months and 24 months follow-up if appropriate.Pregnancy during follow-up with obstetrical outcome.

60 and 120 months follow-up:
Collection of HPV test and Pap smear result via population screening program and sub sequential treatment.Collection of national database on childbirth data on subsequent pregnancies and the following pregnancy outcomes: gestational age, miscarriages, preterm rupture of membranes.

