### Statistical analysis

The main analysis for the primary outcome testing the hypothesis of superiority of nonavalent vaccine as compared to placebo, for preventing CIN II-III recurrence after 24 months will be conducted using a χ^2^ test. Outcome measure for the primary outcome is a relative risk with 95% confidence interval.

Relative risks will also be estimated for secondary categorical outcomes, with 95% confidence intervals and χ^2^ or Fisher’s exact test for significance. Continuous data will be described using means with standard deviation, or medians with interquartile ranges; t-tests or Mann-Whitney U tests will be used as appropriate. Kaplan-Meier curves will be made for time between LEEP, vaccination with active or placebo and CIN II-III recurrence. The curves will be compared using the log-rank test. Quality of Life will be measured at every visit. They will be assessed with Euroqol 5D-5 L questionnaire. Patients from both groups will be analyzed using generalized linear mixed models.

The cost-effectiveness will be assessed by calculating the incremental cost-effectiveness ratio (ICER), defined as the difference in costs, divided by the average change in effectiveness of the vaccine versus a placebo following LEEP treatment. A Budget impact analysis (BIA) will be performed, in accordance with the principles for good practice for BIA, to address the financial stream of consequences in order to assess the affordability of offering the vaccine following LEEP treatment. BIA will compare the likely impact of replacing LEEP by HPV vaccination on national health plan budgets, on hospital level and on assurance level. From the viewpoint of the government, the broad societal perspective and the ‘budgetary framework for care’ will be highlighted. A valid framework (Markov model) will give insight into the budget consequences. We will also perform sensitivity analyses and a ‘most optimistic versus pessimistic’ scenario. If the vaccine has a preventive effect, it will be included in the new national guideline. As a result, the health care insurance can compensate this as regular care.

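### The secondary HPV outcome is worded as any HPV DNA with an unadjusted relative risk; a prespecified vaccine-type analysis, adjusted for baseline type and age stratum, should be added

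*Protocol article*

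**What the plan says.** Under Study objectives and outcome, the protocol article gives the HPV objective as "The effect of HPV vaccination on HPV DNA presence at 6 and 24 months after LEEP". It does not say which types count as positive, or whether a type already present at baseline is handled differently from a new one.

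Under Statistical analysis, one general sentence covers all such outcomes: "Relative risks will also be estimated for secondary categorical outcomes", with 95% confidence intervals and a χ² or Fisher's exact test. No covariate adjustment is stated.

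Four other places bear on the point:

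- **Entry.** Women are enrolled "independent of their hrHPV status" (Abstract, Methods).
- **Vaccine.** It contains nine named types: 6, 11, 16, 18, 31, 33, 45, 52 and 58 (Background).
- **Mechanism.** The Background suggests, as a hypothesis, a stronger immune response after vaccination, and adds that "there ought to be protection against de novo HPV infections".
- **Typing.** The Abstract states "At the start and throughout the study HPV typing, quality of life and cost effectiveness will be tested". Data collection lists "Indication for testing, cytology results, KOPAC-classification, HPV genotype, biopsy result" among the data collected, and the follow-up schedule lists genotype at 6 months ("Cytology results and HPV genotype, QoL (Euroqol 5D-5 L) questionnaire") and again at 24 months.

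**The concern.** A woman who is HPV DNA positive at 24 months may carry the type she had before the LEEP, a vaccine type acquired since, or a type the vaccine does not contain. An unqualified presence outcome counts all three alike. If vaccination acts only on some of them, the others enter both arms at about the same rate and pull the relative risk towards 1.

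What is at stake is how the HPV result can be read. A ratio near 1 for any-type presence would be compatible with no vaccine effect, and also with a real effect on vaccine types or new infections that the remaining infections mask. The Background treats post-treatment immune response and protection against new infection as separate routes, and this outcome as worded cannot distinguish them. The Background also reports its cited retrospective cohort both ways, for recurrence related to vaccine types and for recurrence of any type, but the trial's own HPV objective does not carry that distinction over. The genotype data that would allow it are already collected.

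**Working it through.** **1. The plan's own figure.** The only sample size stated is for the primary outcome (Sample size calculations): 3% v 8%, alpha 0.05, power 0.80, total 646. With the unpooled normal approximation, two-sided,

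n per arm = (1.960 + 0.842)² × (0.08×0.92 + 0.03×0.97) / 0.05² = 322.4, rounded up to 323, so 646 in total.

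This reproduces exactly. No figure is stated for HPV DNA, so 323 evaluable women per arm is used below.

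**2. Dilution seen in the article's own figures.** From the cohort cited in the Background:

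- vaccine-type recurrence: (5/197) / (18/211) = 0.30
- recurrence of any type: (9/360) / (27/377) = 0.35

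The difference is modest, and it concerns recurrence, not HPV DNA.

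**3. Assumed scenarios for HPV DNA.** The article gives no HPV positivity, vaccine-type share or effect on HPV DNA. All of the following are assumptions: any-type positivity on placebo P = 20% or 30%; vaccine-type share s = 50% or 70%; reduction in vaccine-type positivity e = 30%, 40% or 50%; no effect on other types; each positive woman counted as either vaccine-type or other.

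- any-type: P v P(1 − s·e), so RR = 1 − s·e
- vaccine-type: P·s v P·s(1 − e), so RR = 1 − e
- power = Φ(|p₁ − p₂| / √{[p₁(1−p₁) + p₂(1−p₂)]/323} − 1.960)

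Worked example, P = 30%, s = 50%, e = 40%:

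- any-type: 30% v 24%, RR 0.80, standard error 0.0349, 0.06/0.0349 = 1.72, power 41%
- vaccine-type: 15% v 9%, RR 0.60, standard error 0.0255, 0.06/0.0255 = 2.36, power 65%

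The absolute difference is 6 points in both. The gain comes from removing positives that the vaccine is assumed not to affect.

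| P | s | e | Any-type RR | Power, any-type | Power, vaccine-type | Gain (points) |
|---|---|---|---|---|---|---|
| 20% | 50% | 30% | 0.85 | 16% | 28% | 11 |
| 20% | 50% | 40% | 0.80 | 26% | 47% | 21 |
| 20% | 50% | 50% | 0.75 | 39% | 68% | 29 |
| 20% | 70% | 30% | 0.79 | 29% | 38% | 9 |
| 20% | 70% | 40% | 0.72 | 47% | 62% | 15 |
| 20% | 70% | 50% | 0.65 | 67% | 83% | 16 |
| 30% | 50% | 30% | 0.85 | 25% | 41% | 16 |
| 30% | 50% | 40% | 0.80 | 41% | 65% | 25 |
| 30% | 50% | 50% | 0.75 | 59% | 86% | 27 |
| 30% | 70% | 30% | 0.79 | 44% | 55% | 11 |
| 30% | 70% | 40% | 0.72 | 69% | 82% | 13 |
| 30% | 70% | 50% | 0.65 | 88% | 96% | 8 |

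(Gains are taken before rounding.)

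**4. Effect on new infections only.** Assume placebo positivity 25%, a 90% reduction in new vaccine-type infections and nothing else, new infections i = 25-75% of positives, and s = 40-80%. Then any-type RR = 1 − 0.9·i·s, which runs from 1 − 0.9×0.25×0.40 = 0.91 to 1 − 0.9×0.75×0.80 = 0.46. With the pooled-variance version of the test, power for any-type presence runs from 10% to 99%, against 69% to over 99% for new vaccine-type infection. At the low end the expected counts are small: 0.25×0.25×0.40×323 = 8.1 on placebo and 0.8 on vaccine.

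**The case against.** The strongest reply is that the article states an objective and a generic method, not a full definition. It nowhere says that types are pooled on purpose or that genotype will be disregarded. Repeated typing suggests that type-level results may be intended, and the full protocol or SAP, which are not shown, may define them. This stands. A reader might infer from the wording that the genotype data will go unused, and the article does not support that. What remains is the outcome and method as worded, which carry neither a type restriction nor a baseline adjustment.

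A second reply also stands. A reader might conclude that any-type presence is uninterpretable, or should become merely descriptive. With 1:1 randomisation the comparison between arms is unbiased. It is also clinically relevant: a positive HPV result at 24 months leads to colposcopy with no stated limit to vaccine types, and a negative hrHPV test is part of the surrogate for absence of CIN. Any-type presence answers a different question, and a useful one.

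Two further inferences should be resisted. The article does not say that the HPV outcome is there to explain the primary result; it is one secondary objective among several. And possibly incomplete dosing at 6 months is a matter of timing that would affect vaccine-type presence equally, so it is no argument against pooling types.

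Finally, the power figures are wholly assumed and depend on zero effect on other types. The only related data in the article show little dilution (0.30 v 0.35). No power is claimed for this outcome.

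**Conclusion.** The point holds as a minor one. The secondary HPV outcome, as worded and with the one method stated, mixes vaccine with non-vaccine types and persisting with new infections. The comparison is unbiased, but an effect confined to vaccine types or new infections would be attenuated, and the two suggested mechanisms could not be separated.

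The size of the attenuation cannot be derived from the documents. Within the twelve assumed scenarios, power is 16-88% for any-type and 28-96% for vaccine-type positivity, a gain of about 8-29 points. An effect on other types would shrink that gain. The primary outcome, its analysis and the total of 646 (750 with attrition) are untouched.

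**What to change.** - Keep any-type HPV positivity at 6 and 24 months as the clinically relevant comparison.
- Add a prespecified analysis of the presence of any of the nine vaccine types at 24 months, reported as a relative risk adjusted for baseline vaccine-type status and for the age stratum used in randomisation (18-29, 30-44, 45 and older). A log-binomial model, or Poisson regression with robust standard errors, would serve.
- Report, as supportive results, persistence of the same type found at baseline and new vaccine-type infection (type absent at baseline), separately.
- If the full protocol or SAP already contains these definitions, confirming that is enough.

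The cost is a few lines of text and slightly more analysis, with no new sample, test or visit. The wording should be settled before unblinding, so that the choice among HPV definitions cannot follow the results. The drawback is small counts in the persistence and new-infection splits, which should be read by their confidence intervals.

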### Interventions

Patients eligible for participation will be counselled and receive written information. All patients must provide written informed consent prior to participation. After written consent patients will be randomised to either
Nonavalent HPV-vaccine (Gardasil-9®) orPlacebo vaccine (physiological salt solution for injections)

The LEEP should be performed according to guideline for regular care. Preferably, at the day of LEEP the first vaccination should be administered. The first vaccination should be administered at least within 4 weeks after the LEEP. This time window was chosen in particular for logistical reasons, for example with the see and treat method. The second dose should be administered at least one month after the first dose and the third dose should be administered at least 3 months after the second dose. All three doses should be given within a 1-year period. Although studies do not indicate adverse pregnancy outcomes, patients will be asked to use reliable contraceptive during the vaccination period (6 months). Follow-up will be according the Dutch guideline for cervical and vaginal dysplasia (CIN, AIS and VAIN 2015) [25], (see Fig. 1: Flowchart study design). One week after each vaccination, telephonic interview is performed to ask for side effect of the injection.

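### The only repeat-treatment outcome within 24 months counts LEEP alone, although the benefit claimed is less repeat surgery by any method

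*Protocol article*

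**What the plan says.** The secondary objectives (Study objectives and outcome) contain one line on repeat treatment: "Number of LEEP for recurrent CIN".

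The benefit is worded more broadly. The abstract's Background describes fewer recurrences as "therefore leading to a reduction in repeated surgical interventions and side effect like preterm birth". The abstract's Discussion gives the aim as to "prevent residual or recurrent cervical dysplasia and decrease risks of repeated surgical treatment". The main Background says "Re-excision is needed in case of recurrence with an increased risk for adverse events", and names no technique.

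The main Background also says: "The most commonly used method to treat CIN II-III is Loop Electrosurgical Excision Procedure (LEEP". This accepts that other methods are in use.

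In Data collection, the 24-month list asks for "All other cytology test, colposcopy results, LEEP result and HPV genotype test between appointment 6 months and 24 months follow-up if appropriate". No other treatment appears in that list. The list for 60 and 120 months, by contrast, includes subsequent treatment without restricting the method.

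**The concern.** The measure is narrower than the claim. A woman whose recurrence is treated by another excision, by ablation or by hysterectomy has had the repeat surgery that vaccination is meant to prevent, yet she contributes nothing to the outcome.

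The data list has the same limit. If non-LEEP treatments are not recorded up to 24 months, nobody can build the wider outcome at analysis. The trial would then report on repeat LEEP and be read as reporting on repeat surgery. The count would also depend partly on which technique each centre prefers.

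A smaller point concerns the words after LEEP. They do not say whether recurrence is judged by the reason for the procedure or by what the specimen shows. A repeat LEEP done on suspicion, with no CIN in the specimen, could in principle be counted either way.

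**Working it through.** **Step 1: claim against measure**

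| Place in the protocol article | Scope of repeat treatment |
|---|---|
| Abstract, Background | Surgical interventions in general |
| Abstract, Discussion | Surgical treatment in general |
| Background | Re-excision, method not named; LEEP is the commonest method |
| Secondary objectives | LEEP only |
| Data collection, months 6 to 24 | LEEP result only |
| Data collection, 60 and 120 months | Subsequent treatment, method not restricted |
| Discussion (main text) | A second LEEP |

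The two rows that govern what is measured up to 24 months are narrower than the first three, which state the benefit. The short-term data list is also narrower than the long-term one.

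**Step 2: reproduce the plan's own figure**

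Inputs from Sample size calculations: 3% and 8%, power 0.8, alpha 0.050 (taken as two-sided), allocation 1:1. With unpooled variance:

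n per arm = (1.960 + 0.842)² × (0.08 × 0.92 + 0.03 × 0.97) / 0.05² = 7.849 × 0.1027 / 0.0025 = 322.4, rounded up to 323.

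The total is 646, as stated. This figure rests on CIN II-III recurrence, so the repeat-treatment outcome does not enter it.

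**Step 3: what an equal undercount does**

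The documents give no repeat-treatment rate and no share treated by other methods. For illustration only, I assume that repeat-treatment rates equal the planning recurrence rates, that 323 women per arm are analysed, and that the same share m is missed in each arm.

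- Rates counted: a = 0.03 × (1 − m) and b = 0.08 × (1 − m).
- Relative risk: a/b = 0.03/0.08 = 0.375 for every m.
- Power = Φ{[(b − a)√n − 1.960 √(2p̄(1 − p̄))] / √(a(1 − a) + b(1 − b))}, with p̄ = (a + b)/2 and n = 323.
- Standard error of the log relative risk = √[(1 − a)/(na) + (1 − b)/(nb)]. The 95% interval is 0.375 × exp(±1.960 × SE).

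| Share missed | Vaccine events | Placebo events | Relative risk | SE | 95% interval | Power |
|---|---|---|---|---|---|---|
| 0% | 9.7 | 25.8 | 0.375 | 0.368 | 0.18 to 0.77 | 79.7% |
| 10% | 8.7 | 23.3 | 0.375 | 0.389 | 0.17 to 0.80 | 75.2% |
| 20% | 7.8 | 20.7 | 0.375 | 0.414 | 0.17 to 0.84 | 69.9% |
| 30% | 6.8 | 18.1 | 0.375 | 0.443 | 0.16 to 0.89 | 63.8% |

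The power in the first row is just under 80% because this formula pools the variance under the null, whereas Step 2 does not.

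**Step 4: the specimen question**

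Read plainly, the objective gives the reason for the LEEP. The data list for months 6 to 24 takes the LEEP result with no requirement that it show CIN. A CIN-free repeat LEEP would therefore be recorded, and on the natural reading counted. What is missing is a sentence that says so.

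**The case against.** The strongest reply is that much of the rationale concerns LEEP specifically. The abstract ties complications to LEEP and to multiple LEEP treatments, and the main Discussion speaks of recurrence that needs a second LEEP. Hysterectomy does not lead to preterm birth, and the oldest stratum is described as less likely to be fertile. On this view the LEEP count is the right one, and merging procedures would blur the obstetric argument. This stands as a reason to keep the LEEP count. It does not answer the general claim about repeat surgery, which the abstract makes twice.

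A second reply is that a condensed article leaves operational definitions to the full protocol or analysis plan. That is fair for the specimen question. It is weaker for the method, because the article states the outcome and the data item and names LEEP in both.

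A reader might infer three stronger things that the documents do not support:

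- **CIN-free repeat LEEPs are lost.** See Step 4. The remark "This time window was chosen in particular for logistical reasons, for example with the see and treat method" explains the timing of the first injection after the index LEEP, and the no-CIN result category belongs to the one-week report on that same LEEP. Neither describes repeat procedures. At 24 months an abnormal test leads to colposcopy with biopsies.
- **The undercount differs by arm and biases the relative risk.** Doctor and patient are blinded, and nothing shown links the choice of method to allocation.
- **The undercount feeds the cost-effectiveness result.** Costs are collected by questionnaire, and no section makes the LEEP count an input.

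**Conclusion.** The mismatch of method holds. The article claims less repeat surgery and measures fewer repeat LEEPs. As listed, the data up to 24 months may not allow the difference to be recovered.

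Its size cannot be determined from the documents. The 10% to 30% range is an assumption chosen to show sensitivity. With an equal share missed in both arms, the cost is fewer events and wider intervals, with no shift in the relative risk. Power for this outcome would fall by 4.5 percentage points at 10% missed (79.7 − 75.2) and by 15.9 at 30% (79.7 − 63.8). The trial is not sized on this outcome, so these figures illustrate lost information and do not indicate a failed design.

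Whether a CIN-free repeat LEEP counts is a minor ambiguity with a natural answer. Overall this is a worthwhile, inexpensive improvement to a secondary outcome. The primary outcome and the 646 are untouched.

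**What to change.** 1. Define the secondary outcome as the number of women with at least one repeat surgical treatment of the cervix (LEEP, other excision, ablation or hysterectomy) for suspected or proven CIN or worse up to 24 months, whatever the specimen shows. Counting women also suits the relative risks planned in Statistical analysis for secondary categorical outcomes.
2. Report two components beside it: any repeat LEEP, and repeat LEEP with histologically proven recurrence.
3. In the 24-month data list, replace the LEEP result item with any cervical treatment: type, date, indication and specimen result.

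The cost is a change of wording and a small group of eCRF fields. The downside is that the broader outcome takes in overtreatment and hysterectomy, neither of which fits the obstetric argument well. Reporting the LEEP counts separately deals with that. Patient management does not change.
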